### Recruitment

2.8

To conduct this study, the researcher will first obtain permission from the Joint Ethical Committee of the School of Nursing and Midwifery and the School of Rehabilitation at Tehran University of Medical Sciences, as well as permission from the Dean of the School of Nursing and Midwifery. The researcher will then visit the School of Nursing and Midwifery to select samples based on the inclusion criteria. All undergraduate nursing students from 6th semester, which includes two classes, will be considered for the study. Eligible participants will be selected through a census. A list of students will be obtained from the school administration, and students will be invited to participate by the principal investigator during an in‐person meeting. After explaining the study's aims and methods, informed consent will be obtained from all participants. The classes will be randomly assigned to either the intervention group (Class A) or the control group (Class B) using simple randomization. In this phase, further explanations about the study will be provided, and students will be encouraged to follow the study's timeline. To minimize the risk of contamination between the classes and prevent information leakage between the two groups, the control group will be included in the study first, followed by the intervention group.

### Random Allocation

2.9

The allocation of classes to the intervention or control group will be done using simple randomization, specifically through a coin flip. One class will be assigned to the “heads” side, and the other to the “tails” side. After flipping the coin, the classes will be assigned to either the intervention group (Class A) or the control group (Class B).

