**Methods and Analysis:**

This RCT involved a 3‐month scenario‐based ethics training program delivered under faculty supervision, targeting sixth‐semester undergraduate nursing students. Participants (*n* = 48) were randomly assigned to either the intervention group or the control group. Both groups received traditional ethics education, however, the intervention group also participated in two workshops focused on core and derived ethical concepts (e.g., autonomy, confidentiality) utilizing a scenario‐based approach. This was followed by weekly online follow‐ups and discussions conducted via WhatsApp Messenger. The outcomes will be assessed using the Sekerka Professional Moral Courage Questionnaire at four time points: immediately before, immediately after, and at 1 and 3 months postintervention. The questionnaire has demonstrated acceptable validity and reliability in previous studies, with Cronbach's *α* exceeding 0.8, and a value of 0.977 reported in an Iranian validation study. In this study, face validity was confirmed by ten nursing faculty members. The data will be analyzed using *t*‐tests, *χ*
^2^ tests, and ANCOVA to evaluate changes in professional moral courage (SPSS v22, *p* < 0.05).

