### Sample Size

2.7

The sample size for this study was calculated using G*Power software (version 3.1.9.4), based on the standard formula for comparing means between two independent groups:

$$n={\left(Z(\alpha /2)\right)+Z_{\beta })}^{2}\cdot \left(\sigma_{1}^{2}+\sigma_{2}^{2}\right)/\Delta^{2}.$$

The calculation was informed by the findings of a previous study conducted by Hosseini Yazdan Abad Sofla et al. [31], which reported an effect size of 1.18. Using a significance level of 0.05 and a statistical power of 0.95, the required sample size was estimated at 40 participants. To account for an anticipated 20% attrition rate, the sample size was increased to 48 participants, ensuring adequate power to detect the expected effect even with potential dropouts.

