### Statistical Analysis

2.12

The statistical analysis plan and reporting approach in this protocol follow the Statistical Analyses and Methods in the Published Literature guidelines (SAMPL) to ensure transparency, accuracy, and consistency in the presentation of all statistical information. To describe quantitative variables, mean and standard deviation will be utilized, while frequency tables, including percentages, will be employed for qualitative variables. The Kolmogorov–Smirnov test will be used to assess the normality of the data distribution. To compare quantitative and qualitative variables between the two groups before the intervention, the independent *t*‐test and *χ*
^2^ test will be applied, respectively. Additionally, the paired *t*‐test will be used to evaluate the effectiveness of the intervention in the control and intervention groups. Analysis of covariance (ANCOVA) will be conducted to control for the effects of confounding variables. Data analysis will be performed using SPSS software version 22, and a significance level of *p* < 0.05 will be considered statistically significant for all tests.

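### One class per arm is allocated by a single coin flip, yet the trial is described, sized and tested as if students had been randomised independently, so class and calendar period are fully confounded with treatment

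*Protocol article*

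**What the plan says.** **Allocation.** Section 2.8 (Recruitment) states: "All undergraduate nursing students from 6th semester, which includes two classes, will be considered for the study". It continues: "The classes will be randomly assigned to either the intervention group (Class A) or the control group (Class B) using simple randomization". Section 2.9 (Random Allocation) gives the mechanism: "The allocation of classes to the intervention or control group will be done using simple randomization, specifically through a coin flip". Sections 2.6 and 2.8 add that the control class goes through the study before the intervention class, to limit leakage between groups.

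**Description.** The abstract says that the participants (n = 48) "were randomly assigned to either the intervention group or the control group". Section 2.1 and the Discussion call the study a randomised controlled trial and do not mention clusters.

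**Sample size.** Section 2.7 uses the "standard formula for comparing means between two independent groups", with a previous study "which reported an effect size of 1.18". It concludes: "Using a significance level of 0.05 and a statistical power of 0.95, the required sample size was estimated at 40 participants". This is raised to 48 for attrition. No ICC or design effect appears.

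**Analysis.** Section 2.12 plans independent t-tests and chi-square tests for the pre-intervention comparison and paired t-tests within each group. It then says: "Analysis of covariance (ANCOVA) will be conducted to control for the effects of confounding variables". All tests use p < 0.05. ANCOVA is the only post-intervention between-group method named. The limitations paragraph of the Discussion covers online follow-up and unblinded participants, but not the single class per arm.

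**The concern.** One coin flip over two classes gives one randomised unit per arm. The flip decides which class is trained. It does not balance the two classes, and it gives no basis for treating their students as independently allocated.

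The arm indicator and the class indicator are the same variable, so anything that makes one class change differently from the other over the three months is part of the estimated treatment effect. The sequential schedule adds calendar period to the same contrast.

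The causal claim is at stake. A significant ANCOVA result would be read as an effect of scenario-based training, and the Discussion anticipates recommending the approach in Iran and elsewhere. An ordinary difference between two classes, or between two periods, could produce the same result. The 5% level and 95% power in Section 2.7 are not properties of this design.

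**Working it through.** **1. The protocol's own figure.** Inputs from Section 2.7: standardised effect 1.18, two-sided alpha 0.05, power 0.95. A two-sample t-test (noncentral t) needs 20 per arm, 40 in total, with power 0.953. At 19 per arm the power is 0.943. The stated 40 therefore reproduces, but for 40 independent students. The 48 is 40 × 1.2.

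**2. Degrees of freedom.** Two classes minus two arms leaves 2 − 2 = 0 degrees of freedom for between-class variation. Its variance cannot be estimated apart from treatment.

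**3. Variance of the arm difference.** Let σ² be the total outcome variance, m the number of students per class and ICC the share of variance between classes.

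- True variance: 2σ²[ICC + (1 − ICC)/m].
- Variance that the student-level test estimates: 2σ²(1 − ICC)/m, because with one class per arm the residual contains only within-class variation.
- Ratio: k = 1 + m·ICC/(1 − ICC). The true SE is √k times the naive SE.

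**4. Type I error.** With df = 2m − 2, it is P(|T_df| > t_0.975,df / √k).

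**5. Numbers.** The documents give neither the ICC nor the class sizes. The calculation assumes m = 24 (48 split equally) and shows a range of ICCs. For m = 24, df = 46 and the critical value is 2.013.

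| Assumed ICC | k | True SE / naive SE | Type I error |
|---|---|---|---|
| 0 | 1 | 1.00 | 5.0% |
| 0.01 | 1 + 0.24/0.99 = 1.24 | 1.11 | 7.7% |
| 0.05 | 1 + 1.20/0.95 = 2.26 | 1.50 | 18.7% |
| 0.10 | 1 + 2.40/0.90 = 3.67 | 1.91 | 29.9% |

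A simulation at ICC 0.05 and m = 24 gave 18.6%, in agreement with the formula. With 20 evaluable students per class, the type I errors are 7.3%, 16.6% and 26.6% at ICCs of 0.01, 0.05 and 0.10.

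**6. More students do not help.** As m grows, the true SE falls only to σ√(2·ICC), which is 0.32σ at ICC 0.05 and 0.45σ at ICC 0.10, while the naive SE goes to zero. The type I error therefore rises with class size, for example from 16.6% at m = 20 to 18.7% at m = 24 when the ICC is 0.05.

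**7. The usual design effect is not the right multiplier here.** √[1 + (m − 1)·ICC] gives 1.47 and 1.82 at ICCs of 0.05 and 0.10, against the required 1.50 and 1.91. It presumes a residual variance that includes the between-class part. Using it would leave the type I error at 5.6% and 6.2%.

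**The case against.** Class allocation has a stated reason. The intervention shares materials and discussion by WhatsApp for three months, and the protocol keeps the groups apart, control first, to prevent leakage. Sections 2.8 and 2.9 disclose the class allocation openly, and a coin flip is a random act. Both classes share a school, semester and curriculum, so the ICC may be small, and baseline adjustment may absorb stable class differences. All of this is fair. It supports comparing classes. It does not support describing or testing the result as individual randomisation, and no later analysis plan can create replication that the allocation lacks.

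Three stronger readings are tempting, and the documents do not support them.

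- **A reader might infer that every p-value and confidence interval in the trial is too narrow.** Section 2.12 names no confidence interval. The within-group paired t-tests are not between-arm comparisons, and the calculation does not address them. At an ICC of exactly zero, the between-group test has its nominal level as far as clustering is concerned.
- **A reader might infer that the abstract promises 1:1 randomisation of students within class.** It says only that participants were randomly assigned. It is imprecise and has to be aligned with Section 2.9; it does not specify another design.
- **A reader might apply the tabulated error rates to ANCOVA without qualification.** They are derived for a two-sample t-test. They carry over to ANCOVA only if the ICC is that of the covariate-adjusted outcome, which may be smaller than the raw one.

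**Conclusion.** The point holds and needs correction. With one class per arm, class and calendar period are fully confounded with treatment, and the description, sample size and test level all presume independent students. The confounding and the zero degrees of freedom follow from the protocol's text alone and rest on no assumption.

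The size of the error does rest on assumptions: 24 students per class, and an ICC of the covariate-adjusted outcome between 0.01 and 0.10. On these, the nominal 5% between-group test has a true type I error of about 7.7% to 29.9%, and its SE is too small by a factor of 1.11 to 1.91. These figures cover clustering only. The effect of running the arms in different periods comes on top and cannot be quantified from the documents.

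**What to change.** - **Abstract, Sections 2.1 and 2.9, Discussion:** describe the study as a two-class controlled comparison with one cluster per arm. Replace the abstract's statement that participants were randomised with a statement that classes were allocated.
- **Section 2.7:** state that the 95% power and 5% level hold only if students are independent (ICC = 0).
- **Section 2.12:** make the baseline-adjusted difference the estimate. Show its 95% confidence interval as a sensitivity display at assumed ICCs such as 0.01, 0.05 and 0.10, multiplying the SE by √[1 + m·ICC/(1 − ICC)] and stating the m used. Do not rest the hypothesis on the naive p < 0.05. The display shows how fragile the result is; it does not repair the design.
- **Limitations:** state that class and calendar period are confounded with arm, and that the ICC-widened interval does not cover the period effect.

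The cost is wording and a few lines of analysis. The real price is a less favourable conclusion.

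Randomising students within class is not part of the required fix. It trades against the contamination that the protocol deliberately designed against, and it does not fit the control-first schedule. It may also no longer be possible, since the abstract reports assignment in the past tense.

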### Blinding

2.10

Due to the nature of this intervention, it will not be possible to blind the participants or the intervening party. However, the outcome assessor will work independently from the interventionist and will not know which group the participants belong to. The outcome assessors, data entry personnel for SPSS, and epidemiological consultants will be blinded and trained to ensure they do not inquire about whether participants have received the intervention. Additionally, participants will be instructed not to discuss their activities with the outcome assessors.

### Data Management

2.11

The demographic questionnaire will be completed by both the control and intervention groups after obtaining written consent. The intervention and control groups will be assessed on the dependent variable (Professional Moral Courage) immediately before the training workshop, immediately after its completion, 1 month later, and 3 months after the intervention. The standardized Professional Moral Courage Questionnaire by Sekerka et al. [14] will be completed in person and printed format. To minimize and prevent data loss, students will be encouraged and monitored to complete the questionnaires fully at each stage. Additionally, the outcome assessor will receive training to ensure the accurate and complete collection of data. Data entry into SPSS version 26 will be performed by a trained researcher, and the accuracy of the entered data will be verified by another member of the research team. To maintain participant confidentiality, the data will be stored using anonymous code numbers. Finally, data analysis will be conducted by an epidemiologist.

### Statistical Analysis

2.12

The statistical analysis plan and reporting approach in this protocol follow the Statistical Analyses and Methods in the Published Literature guidelines (SAMPL) to ensure transparency, accuracy, and consistency in the presentation of all statistical information. To describe quantitative variables, mean and standard deviation will be utilized, while frequency tables, including percentages, will be employed for qualitative variables. The Kolmogorov–Smirnov test will be used to assess the normality of the data distribution. To compare quantitative and qualitative variables between the two groups before the intervention, the independent *t*‐test and *χ*
^2^ test will be applied, respectively. Additionally, the paired *t*‐test will be used to evaluate the effectiveness of the intervention in the control and intervention groups. Analysis of covariance (ANCOVA) will be conducted to control for the effects of confounding variables. Data analysis will be performed using SPSS software version 22, and a significance level of *p* < 0.05 will be considered statistically significant for all tests.

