Scenario‐based training, as an interactive approach, enhances students' decision‐making skills and prepares them to face ethical challenges in difficult situations [21, 22]. While previous research has focused on issues like moral distress and moral courage among nurses, few studies have examined these issues among nursing students. Understanding the factors that influence students' moral courage can help healthcare and educational stakeholders design appropriate interventions to enhance moral courage among students [22, 23].

Innovative teaching methods, such as scenario‐based training, which remains limited in Iran, may potentially improve students' ethical skills and abilities. This approach can guide students toward a deeper understanding of ethical concepts, strengthen professional behaviors, and foster an ethical culture in educational and professional settings [21]. By presenting realistic scenarios, it is possible to enhance students' moral resilience against the pressures and challenges of the healthcare system [24].

Based on the literature review, moral courage is essential for professional decision‐making in the nursing profession; however, traditional teaching methods fail to prepare students to address ethical challenges adequately. Scenario‐based training may have the potential to enhance students' ethical competencies. Despite the importance of this issue, to the best of our knowledge, no study has yet examined the impact of scenario‐based training on nursing students' professional moral courage. This study aims to fill this gap by investigating how scenario‐based training of moral concepts compares with traditional teaching methods. Accordingly, this study aims to investigate the impact of scenario‐based moral concepts training on the professional moral courage of nursing students, with the hypothesis that scenario‐based ethics training will significantly increase the professional moral courage of nursing students compared to traditional teaching methods.

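### Section 2.12 assigns the evaluation of effectiveness to paired t-tests within each group, and nowhere makes the between-group contrast decisive, although the hypothesis and the sample size are between-group

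*Protocol article*

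**What the plan says.** The Introduction states a comparative hypothesis: the training "will significantly increase the professional moral courage of nursing students compared to traditional teaching methods".

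The Sample Size section (2.7) is built on the same contrast, "based on the standard formula for comparing means between two independent groups", from a previous study "which reported an effect size of 1.18". It arrives at 40 students, raised to 48 for dropout.

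The Statistical Analysis section (2.12) then gives each method a role:

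- Independent t-test and chi-square test: "To compare quantitative and qualitative variables between the two groups before the intervention".
- Paired t-test: it "will be used to evaluate the effectiveness of the intervention in the control and intervention groups".
- ANCOVA: "Analysis of covariance (ANCOVA) will be conducted to control for the effects of confounding variables".

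The abstract lists t-tests, chi-square tests and "ANCOVA to evaluate changes in professional moral courage", without ranking them.

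The Data Collection section (2.6) schedules the same questionnaire in both groups at baseline and at three later times: just after the workshop, at 1 month and at 3 months.

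**The concern.** The hypothesis asks whether the trained students end up with more moral courage than the others. A paired t-test in one arm asks whether that arm changed over time. Running it in both arms gives two answers to the second question and none to the first. A significant result in one arm beside a non-significant result in the other is not evidence that the arms differ, and two significant results leave the treatment effect unestimated.

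This matters because change common to both arms is plausible here. The same 15 items are answered four times, the students are not blinded, and their education continues during the study. If effectiveness is read from within-arm significance, such change can be credited to the training. The protocol would also have been sized for one test and judged by another.

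**Working it through.** **1. Which test was the trial sized for?** Inputs from section 2.7: effect size 1.18, power 0.95, significance level 0.05. The printed formula uses Z(α/2), so the test is two-sided.

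- Printed normal formula, in SD units: n per arm = (1.960 + 1.645)² × 2 / 1.18² = 18.7, so 19 per arm and 38 in total.
- Noncentral t, two independent groups: with 20 per arm the noncentrality is 1.18 × √(20/2) = 3.73 on 38 degrees of freedom, and power is 0.953. That gives 40 in total, the stated figure.
- One-sided versions give 32 (normal) or 34 (t) and do not reproduce 40.

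The 40 is therefore the size of a two-sided between-group t-test.

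**2. Which test is tied to effectiveness?** In section 2.12 the word is attached to the paired t-test alone. The independent t-test is confined to baseline. ANCOVA is assigned to confounders there and to changes in the abstract. No sentence says that the difference between arms decides the question.

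**3. What can within-arm testing do when the training has no effect?** The protocol gives neither a retest change nor a pre-post correlation, so these are assumptions: both arms rise by δ SD, the pre-post correlation is r, each arm has n = 24 (48/2), and students are independent.

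- Standardised paired change: d_z = δ / √(2(1 − r)).
- Noncentrality of each paired t-test: d_z × √n on n − 1 = 23 degrees of freedom.
- Worked case, δ = 0.3 and r = 0.6: d_z = 0.3/√0.8 = 0.335, noncentrality = 0.335 × √24 = 1.64, chance of significance in either arm = 0.35.
- Chance that the intervention arm is significant and the control arm is not: 0.35 × (1 − 0.35) = 0.23.

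| Shared rise (SD) | r | Intervention arm significant | Intervention up and significant, control not |
|---|---|---|---|
| 0 | 0.5 or 0.7 | 0.050 | 0.024 |
| 0.2 | 0.5 | 0.156 | 0.130 |
| 0.2 | 0.7 | 0.228 | 0.176 |
| 0.3 | 0.5 | 0.291 | 0.206 |
| 0.3 | 0.7 | 0.444 | 0.247 |
| 0.5 | 0.5 | 0.650 | 0.227 |
| 0.5 | 0.7 | 0.857 | 0.122 |

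For rises of 0.2 to 0.5 SD the pattern in the last column occurs in 12% to 25% of trials. With 20 per arm the range is also 12% to 25%. The comparison figure is 2.5%, the upper tail of a two-sided 5% test between arms.

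**4. What does a between-group test do under the same conditions?** A shared rise cancels in the contrast. In simulation (24 per arm, rises of 0, 0.3 and 0.5 SD, r of 0.5 and 0.7), ANCOVA with arm and baseline score rejected in 4.8% to 5.7% of trials. Its residual variance is 1 − r² of the unadjusted variance: 0.75, 0.64 and 0.51 at r = 0.5, 0.6 and 0.7. The reduction is therefore 25%, 36% and 49%. Even without adjustment, power at the protocol's effect size is 0.953 with 20 per arm and 0.979 with 24. These figures treat students as independent and include no class or period effect.

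**The case against.** The strongest reply is that a between-group method is already planned. The abstract ties ANCOVA to changes in moral courage, the sample size shows which contrast was intended, and ANCOVA with arm as a factor would test it. The choice of covariates and the exact contrast may properly sit in an analysis plan that is not shown. This stands in part: a reader might infer that the protocol has no between-group analysis of the outcome, and the documents do not support that. It does not remove the point, because section 2.12 does more than leave detail open. It assigns effectiveness to a test that cannot address the hypothesis, and nothing ranks ANCOVA above it.

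A reader might also infer that the training will be credited with retest or maturation change. That is too strong. The protocol states no rule that significance in one arm and not in the other means success, a shared rise might be visible in the control arm's own test, and with no shared change each paired test holds its level. The 12% to 25% range illustrates a risk under assumed inputs; it is not this trial's error rate.

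Finally, the remedy has a limit. Sections 2.8 and 2.9 allocate one whole class to each arm by coin flip, and section 2.6 has the control class finish first. A between-group ANCOVA would compare two classes in two periods. This stands, and it belongs in the fix.

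**Conclusion.** The point holds as a misassigned test of effectiveness. Section 2.12 evaluates effectiveness within arms, while the hypothesis and the reproduced sample size of 40 are between-group. ANCOVA is listed without being made decisive. That within-arm significance does not test the hypothesis needs no assumption. The size of the risk does: 12% to 25% against about 2.5% in one direction requires a shared rise of 0.2 to 0.5 SD, a correlation of 0.5 to 0.7, no training effect, independent students, and a conclusion drawn from comparing the two paired results. It should be corrected before analysis, because it concerns which contrast answers the trial's only stated hypothesis.

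**What to change.** In section 2.12, and in matching words in the abstract:

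- Make the primary test of effectiveness the between-group difference in Professional Moral Courage score at one named time point among the three after baseline. Estimate it by ANCOVA with arm and baseline score, and report an adjusted mean difference with a 95% confidence interval.
- Report within-arm changes descriptively only, and remove the paired t-test as the test of effectiveness.
- State as a limitation that, with one class per arm and the classes run in sequence, this contrast cannot separate the training from class or period effects, and that its confidence interval does not reflect them.

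The cost is wording. All the measurements needed are already scheduled in both groups, and on the protocol's own assumptions the between-group test needs no more students. The change corrects the contrast; it does not cure the confounding with class and period.

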### Data Collection

2.6

In this study, data will be collected using two questionnaires: a demographic information questionnaire and the Professional Moral Courage questionnaire by Sekerka et al. [14]. The demographic information of the students will be gathered through a written questionnaire at the beginning of the study. Data on the dependent variable (Professional Moral Courage) will be collected immediately before the workshop, immediately after the workshop, 1 month later, and 3 months after the intervention. Both the intervention and control groups will be assessed for this variable, and they will complete the standardized Professional Moral Courage questionnaire by Sekerka et al. [14] in person using printed paper and pencil.

To prevent information leakage and sample contamination, the control group will complete the study first, followed by the intervention group.

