## Consent

Written consent will be obtained from all students, and they will be fully informed of their rights to voluntary participation and the ability to withdraw at any stage of the study. Data will be stored confidentially using anonymous codes. The contact information of the researcher will be provided to the students in case they have any questions or need guidance.

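### The analyses named in section 2.12 leave early leavers' scores out of the later contrasts; a repeated-measures model would use them, with modest gains in precision and in protection against arm-specific dropout

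*Protocol article*

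**What the plan says.** All references are to the protocol article.

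- **Visits (2.6 Data Collection; repeated in 2.11 Data Management).** Both groups complete the questionnaire "immediately before the workshop, immediately after the workshop, 1 month later, and 3 months after the intervention". No visit is named as the primary time point.
- **Attrition (2.7 Sample Size; Consent).** "To account for an anticipated 20% attrition rate, the sample size was increased to 48 participants", which is described as "ensuring adequate power to detect the expected effect even with potential dropouts". Students also keep "the ability to withdraw at any stage of the study".
- **Prevention (2.11).** Students are encouraged and monitored to complete every questionnaire, and the assessor is trained in complete collection.
- **Analysis (2.12 Statistical Analysis).** Baseline comparisons use t- and chi-square tests. The paired t-test judges effectiveness within each group, and "Analysis of covariance (ANCOVA) will be conducted to control for the effects of confounding variables". No repeated-measures model is named, and no rule is given for students with incomplete data.
- **Loss that can arise in one class only (2.3.2 Exclusion Criteria).** A student who misses a scheduled workshop is excluded or withdrawn. Only the intervention class has workshops.

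**The concern.** A paired t-test needs both scores of the pair, and an ANCOVA of a later score needs that later score. Consider a student who completes the baseline, post-workshop and 1-month questionnaires and then leaves. On observed data this student adds nothing to the 3-month between-class estimate, although the two follow-up scores already in hand predict the missing one. A student who leaves after the post-workshop visit is lost to both later contrasts.

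The step in section 2.7 from 40 to 48 students protects precision. It cannot remove bias if those who leave differ from those who stay, and differ in another way in the other class. The design makes class-specific loss conceivable: only the intervention class carries three months of weekly scenario work, participants are not blinded, and the control class goes through the study first, at a different time. If low post-workshop scorers left the intervention class alone, the students remaining there at 3 months would score too high, and the ANCOVA estimate would favour the training.

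**Working it through.** **1. Reproduce the plan's own figures.** Inputs from section 2.7: "which reported an effect size of 1.18"; "Using a significance level of 0.05 and a statistical power of 0.95". The printed formula uses Z(α/2), so the test is two-sided.

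- Normal approximation: n per arm = (1.960 + 1.645)² × 2 / 1.18² = 18.67, so 19 per arm and 38 in total.
- Noncentral t (the G*Power method): 20 per arm, 40 in total, power 0.953. This agrees with "the required sample size was estimated at 40 participants".
- Inflation: 40 × 1.2 = 48. Dividing by 0.8 would give 50, which is a separate small point.
- After 20% loss: 48 × 0.8 = 38.4. At 19 per arm, power is 0.943 against the target 0.95. The expected loss therefore costs little power, and the question is one of bias and efficient use of the data.

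**2. Simulation at the trial's size.** From the protocol: four visits, 48 students (taken as 24 per class, since no ratio is stated) and about 20% lost. Assumed, because the protocol does not give them: normal scores with SD 1, baseline-to-follow-up correlation 0.5, correlation between follow-ups 0.6 to 0.8, and monotone dropout after the post-workshop visit. There were 6,000 trials per scenario, so the Monte Carlo error of a mean is about 0.282/√6000 = 0.004 SD.

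The comparison is between observed-data ANCOVA at 3 months and the maximum-likelihood estimate for monotone missing data, which corresponds to a repeated-measures model. In the middle rows, dropout in the intervention class depends on the last observed score and control dropout is random.

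| Scenario | ANCOVA | Repeated measures |
|---|---|---|
| Random dropout, both classes: SE | 0.282 | 0.272 |
| Intervention class only, log-odds 0.5 per SD: bias | +0.046 | +0.003 |
| Intervention class only, log-odds 1.0: bias | +0.084 | +0.003 |
| As above, no true effect, follow-up correlation 0.8: bias | +0.117 | +0.001 |
| Same row: root mean squared error | 0.306 | 0.271 |
| Same mechanism in both classes: bias | about 0.005 or less | about 0.005 or less |

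- Precision: (0.272/0.282)² = 0.93, about 7% less variance. A repeat run gave SEs of 0.280 and 0.268.
- Bias relative to the standard error: 0.046/0.282 = 0.16 up to 0.117/0.282 = 0.41.
- Bias relative to the design effect of 1.18: 0.046/1.18 = 4% up to 0.117/1.18 = 10%.
- With no true effect, a shift of about 0.4 SE would move a two-sided 5% test to Φ(−1.56) + Φ(−2.36) = 0.059 + 0.009, about 7%.

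**3. Large-sample check under different assumptions.** 400,000 per arm, one common correlation between all visits (0.3, 0.5 or 0.7), true 3-month effect 1.18, about 20% dropout after the post-workshop score.

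- Random dropout, or the same mechanism in both classes: ANCOVA gives 1.18, no bias.
- Low post-workshop scorers leave the intervention class only: 1.22 to 1.23, bias about +0.04.
- Opposite mechanisms in the two classes: 1.26 to 1.27, bias about +0.08 to +0.09.
- An estimator that also uses leavers' post-workshop scores: 1.18 in every scenario.

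Both exercises agree on the direction, on the order of magnitude, and on the condition that the bias needs: dropout driven differently in the two classes.

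**The case against.** The strongest reply is that section 2.12 does not say what happens to leavers. A reader might infer that the plan can analyse completers only, or that it discards leavers' data by rule. The text supports neither. No complete-case rule is written, and ANCOVA after imputation would be compatible with the wording. An article may also leave missing-data handling to a fuller document, so silence on it is not the complaint here. What stands is narrower: the methods named do not by themselves link the visits, and the four-visit data support one that does.

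Other parts of the reply also stand:

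- Leavers' scores are not lost altogether. They count at every visit completed.
- The paired t-test is within-group, so it gives no between-class contrast to bias. The bias argument concerns ANCOVA alone.
- Section 2.7 is not the only provision for attrition; section 2.11 contains prevention measures.
- The protocol does not say that low scorers will leave the intervention class. The weekly tasks run on WhatsApp while the outcome is a paper form completed in person, so ignoring a task is not the same as missing a questionnaire.
- The one class-specific loss that is written down, withdrawal after a missed workshop, would usually occur before any later score exists. The repeated-measures model would not recover those students either.
- One class per arm is a larger problem, and this change leaves it untouched.

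These points limit the size of the concern. They do not show that the stated analysis makes as good use of the planned data as the alternative.

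**Conclusion.** The point holds as a recommended improvement, with modest stakes. For an outcome measured at four visits with 20% attrition expected, the named methods, run on observed data, leave usable earlier scores out of the later between-class contrasts.

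Under random dropout the cost is small: an SE of about 0.28 against 0.27 SD. If low scorers leave the intervention class only, the 3-month ANCOVA estimate is biased upward by about 0.05 to 0.12 SD in the trial-size simulation and about 0.04 SD in the large-sample check. The repeated-measures model stays within 0.01 SD. If dropout is random or works alike in both classes, neither method is materially biased.

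The correlations and dropout mechanisms are assumptions, and the 3-month visit is used because it is the last and most exposed to loss, not because the protocol makes it primary. It would go too far to infer that the trial's 3-month result will be biased, or that attrition leaves it underpowered: the first depends on an undocumented mechanism, and power at 19 per arm is still 0.943.

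**What to change.** In section 2.12, make the between-class effectiveness analysis one linear mixed model for repeated measures (SPSS MIXED, REML, unstructured covariance):

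- Outcomes: the post-workshop, 1-month and 3-month scores.
- Terms: class, visit, class-by-visit and baseline score by visit.
- Students: everyone with a baseline score and at least one later score.
- Report: the class difference at each visit, with a small-sample degrees-of-freedom correction available in the software version used. Section 2.12 names version 22 and section 2.11 names version 26, so settle the version first.
- Keep observed-data ANCOVA as a sensitivity analysis and the paired t-tests as descriptive only.

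In section 2.7, say that enlarging the sample protects precision and does not guard against bias from dropout.

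The cost is a paragraph of wording and a little more analysis work in software already named, with no new data, visits or staff. The downside is that the model assumes dropout depends on observed scores, and it estimates a 3 × 3 covariance matrix from about 48 students. It does not recover students withdrawn under section 2.3.2 before any later score, and it does not address the allocation of one class per arm.
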